#### MDS-UPDRS part three motor score in the practically defined OFF medication state

Whereas the analysis of the 96-week scores according to randomisation group will represent the primary outcome for this trial, differences emerging at 48 weeks and also the difference between scores at 48 weeks and 96 weeks will be important secondary outcomes.

##### MDS-UPDRS part 1, 2, 3 and 4 on medication scores

Part 3 of the MDS-UPDRS as well as the other elements (part 1, 2 and 4) of the scale will also be evaluated in the presence of conventional PD medication (ON state) to evaluate any change in some of the NMS of PD, activities of daily living and the complications of chronic PD treatment.

##### Montreal Cognitive assessment

This scale is a validated global measure of cognitive ability. This will be assessed in the ON medication state.

##### Timed tests

Participants will be asked to perform a Sit-stand-walk timed test in both the OFF medication and ON medication state. The timed Sit-stand-walk test will incorporate time taken from seated position to stand and walk 10 metres, turn and return to original seated position.

##### Unified Dyskinesia Rating Scale

This is considered to be the most useful and objective way of quantifying dyskinesia severity. This will be assessed in the ON medication state.

##### Patient Health Questionnaire-9

This scale allows for self-quantification of depression severity. This will be assessed in the ON medication state.

##### Non-Motor Symptom Scale

This validated scale is a tool to collect data on the frequency and severity of 30 NMS sometimes experienced by PD patients. This will be assessed in the ON medication state.

##### The Parkinson’s Disease Questionnaire

This is the standard disease specific measure of quality of life in PD comprising 39 questions. It has been extensively validated in previous studies.

##### Levodopa equivalent dose

To facilitate comparisons between patients taking different regimes of conventional PD medications, a set of conversion factors have been used to convert each of the commonly used PD medications to an LED of each of their medications can then be summed for interpatient/intergroup comparisons.^20^

##### EQ-5D-5L

This is a simple, 5 question form and visual analogue scale that allows calculation of quality-adjusted life-years to enable health economic analyses to be performed.

##### The Client Service Receipt Inventory

Health and social care resource use. Self-completed healthcare, social care and paid/unpaid carer resource use questionnaire asking about primary and secondary care resource use relevant to Parkinson’s and impact on carers in the past 6 months.

#### Three-day Hauser diary

A 3-day Hauser diary of PD state (time-on, off, troublesome dyskinesia, non-troublesome dyskinesia, asleep). Diary data allow quantification of the amount of time during a 3-day period that patients spend in the varying states of movement ability.

### Ancillary studies

There are four optional substudies linked to the main trial:

Genetics substudy: To try to identify genetic markers that may be associated with subtypes of PD or variation in treatment responsiveness.Cerebrospinal Fluid (CSF) substudy: To determine whether any CSF changes associated with PD are influenced by exposure to exenatide. These may include alpha synuclein monomers or oligomers, neuroinflammatory markers, and exosomal contents.Remote Monitoring of PD Symptoms substudy: To help determine whether measurement of PD symptoms using digital technology may be a more sensitive measure of change with active drug vs placebo compared with the MDS UPDRS 3 in the OFF and ON medication states. This will form two separate measurements comprising (1) home-based smartphone and (2) real-world gait/walking activity monitoring.^21–23^ This aims to generate precision data, providing person-specific distributions of outcomes and may be able to better delineate baseline clinical features.DaTSCAN (Imaging substudy): To determine if change in dopamine transporter availability in the caudate and putaminal nuclei as measured by quantitative DaTSCAN signal is influenced by exposure to exenatide compared with placebo.

### Visits

The overall progression of assessments are summarised in figure 1. While we expect to undertake all assessments in respective clinical units, provision has been made in line with INCLUDE guidance for the possibility of home visit assessments to be performed when patient specific situations (eg, inability to travel due to coronavirus restrictions, worsening ‘OFF’ state over progression of trial) necessitate this. We hope that this provision will aid overall trial retention while enhancing recruitment of patients from typically less well represented demographics (eg, rural geographical regions, patients lacking private travel facilities).

### Screening visit

Written informed consent to enter and be randomised into the trial will be obtained from participants, after explanation of the aims, methods, benefits and potential hazards of the trial and before any trial-specific procedures are performed or any blood is taken for the trial. Patients will be screened using the history of their PD, supported by any available clinical correspondence according to usual standard of care.

The collection of the following scales will evaluate patient eligibility: Montreal Cognitive Assessment (MoCA), PHQ-9, as well as blood tests (full blood count, urea and electrolytes, creatinine, liver function tests, Haemoglobin A1c, C-peptide, coagulation, serum amylase, thyroid function tests, blood glucose, insulin and lipid profile, and a pregnancy test for women of childbearing potential). Tests can be repeated between screening and baseline visits, if required to confirm eligibility. Abnormalities detected that warrant further management for example, newly diagnosed diabetes will be referred for appropriate medical evaluation.

Patients recruited to the DATSCAN substudy will have imaging performing prior to their baseline visit.

### Baseline visit and randomisation

Previously defined primary and secondary outcome measures will be performed in the ‘ON’ and ‘OFF’ states as outlined below. Patients’ LED will be noted. Randomisation to either exenatide or placebo will be administered using a centralised, web-based system (www.sealedenvelope.com). All assessments related to sub-studies will also be performed prior to trial medication administration.

### Assessment procedures

After the screening visit, the named site clinical staff member will call the participant to remind them of the need to stop taking their regular PD medication prior to their next trial visit and to attend in a fasted state (prior to visits 2, 4, 6, 8, 10). The MDS-UPDRS part 3 and Timed Walk assessments will be initially performed in the OFF state. This assessment in both the ‘OFF’ and ‘ON’ states will be performed with video recording to facilitate the possibility of a re-review if necessary. Remote monitoring assessments will be conducted at this point at selected sites in patients consenting to participate in this substudy. While waiting for medications to work, participants will self-complete the MDS-UPDRS parts 1, 2 and 4, Parkinson’s Disease Questionnaire-39, EQ-5D-5L and Client Service Receipt Inventory. The MDS-UPDRS part 3 and Timed Walk assessments will be repeated 1 hour after the participant has taken their routine medications—the ON medication state. After completion of the MDS-UPDRS and Timed Walk assessments in the ON medication state, each participant will be assessed using the MoCA, NMS scale, Unified Dyskinesia Rating Scale and PHQ-9. This will occur in alternate postrandomisation assessments (at visits 2, 4, 6, 8, 10). At selected centres participants in the CSF substudy will have a CSF sample taken via lumbar puncture. Ten weeks after the last trial medication administration, a staff member will call the participant to collect details of any AEs that have occurred after the participant stops taking the trial medication. Participants will complete the 3-day Hauser Diary prior to visits 2, 6 and 10 and return the diary back to the research team at the respective study visits. At each of the visits 2, 4, 6, 8 and 10, a blood sample will be collected and processed for storage for future analysis.

The DaTSCAN imaging substudy will be performed at the UCLH site on all consenting substudy participants; scans will be performed prior to visit 2 and after visit 10.

The option for performing a remote assessment will be provided to patients for safety monitoring visits in view of the coronavirus pandemic.

### Intervention

Each dose of exenatide 2 mg (powder and solvent for prolonged release, suspension for injection, prefilled pen) is supplied as a single use injection pen for subcutaneous administration by the patient on a weekly basis. The placebo (inactive powder and solvent for prolonged release, suspension for injection, prefilled pen) is supplied as an identical injection pen for subcutaneous administration by the patient on a weekly basis. The trial medication will be refrigerated and stored at 2°C–8°C. Both exenatide and placebo will be supplied by AstraZeneca as unlabelled prefilled pens in bulk and in accordance with Good Manufacturing Practice (GMP). Labelling, packaging and release of packed trial medications will be managed by the Sponsor’s contracted company following GMP. The labels will be prepared in accordance with GMP Annex 13 (online supplemental material 1) requirements for labelling and local regulatory guidelines. The trial medications will be released ahead of trial use.

10.1136/bmjopen-2020-047993.supp1Supplementary data

Site trial staff will be trained on the use of exenatide using an online teaching video, accompanying product literature and the investigator’s brochure. Patients will be taught how to perform the subcutaneous injections by the clinical trial team (TT) using the online video, demonstration packs and written literature. They will be told about common adverse reactions previously reported, for example, nausea, vomiting, diarrhoea and weight loss by the clinical TT, and will be advised on the processes for safety reporting. In the event that exenatide injections will be administered by caregivers (eg, spouse), their willingness to perform this will be documented and they will be trained using the online teaching video. It will also be ascertained that the caregiver either lives with the PD patient or confirms their willingness to meet with the PD participant on a weekly basis to administer the injections for the 96-week period of the trial.

Patients who meet eligibility criteria at the screening visit will be randomly assigned to receive 96 weeks of double-blind treatment with either exenatide or placebo (2 mg once weekly) in a 1:1 ratio. The first dose will be administered by the patient in clinic following injection training and subsequent injections will be at home. Injections will be self-administered by the participants, or administered by their carer, into the participants’ abdomen, arm, thigh or buttocks every 7 days. Participants will be provided with a link to the injection pen training video and an Research Ethics Committee approved injection administration training sheet.

### Sample size

The sample size is based on the detectable effect size (primary outcome is the MDS-UPDRS motor subsection in the OFF medication state) for a two-arm (exenatide vs placebo) parallel-group trial design. The calculations assume a common SD of 13.5, and a correlation of 0.70 between baseline and follow-up MDS-UPDRS measurements. These estimates are reasonable based on data from the previous exenatide-PD trial.^14^ On this basis, 160 evaluable participants divided equally between the two groups is sufficient to detect a difference of 5.0 MDS-UPDRS part 3 points in the OFF medication state between the two groups adjusting for baseline MDS-UPDRS part 3 OFF scores, with 90% power and at a significance level of 0.05. Assuming 20% attrition (withdrawal/lost to follow-up), 200 participants will be recruited. Participants who withdraw from the trial will not be replaced. Participants who withdraw from trial treatment should remain in the trial for the purpose of follow-up and data analysis. This effect size is a reasonable expectation based on the previously collected pilot data and would represent a clear demonstration of the efficacy of exenatide on the motor severity of PD.

It is also anticipated that the difference in scores in the ON medication state will be greater at 96 weeks than at the earlier time points. The expected rate of change in PD severity in the first 5 years after PD diagnosis in the ON medication state is 1 MDS-UPDRS part 3 point per year. A predicted advantage of 2 points in ON scores over 96 weeks would thus equate to an advantage in the rate of disease progression above and beyond that achievable with conventional dopaminergic medication and would be a further clear signal that continued use of exenatide is consistent with not only long-term disease modifying effects, but even demonstration of a small change of 2.5 points in the MDS-UPDRS motor score would constitute a clinically important difference^24^ and potentially an advantage in day to day functional impairment and overall improvement in quality of life in the short term.

### Statistical analysis

A full statistical analysis plan will be written and approved by the TSC prior to database lock. All analyses will be undertaken according to a modified intention-to-treat principle in accordance with the randomised intervention. The threshold for the analysis population will be participants who complete 12 weeks on treatment and for whom outcomes are available.

Primary outcome analysis will evaluate the impact of treatment allocation (exenatide or placebo) on the difference between MDS UPDRS part 3 OFF medication scores at 96 weeks follow-up adjusting for baseline. The analysis will use a mixed-model approach incorporating information from all follow-up visits that adjusts for baseline Hoehn and Yahr status and the baseline raw value of each outcome measurement. Site will be included as a random effect to account for variability in outcomes between sites, and a random patient/subject effect will accommodate the correlation between repeated outcome measures on the same patient. A significance level of 5% will be used to judge significance for the primary outcome measure.

A planned secondary analysis will compare the difference in MDS-UPDRS part 3 OFF medication scores according to randomisation allocation at 96 weeks, with the scores at 48 weeks. An increase in the advantage at 96 weeks compared with 48 weeks would be evidence that the active drug was slowing down disease deterioration rather than having symptomatic effects only. This could translate to a major population advantage in terms of reduction of morbidity and mortality.

Analyses of the remaining secondary/exploratory outcomes will be undertaken similarly for the difference between groups according to treatment allocation at 48 and 96 weeks follow-up adjusting for baseline values of each outcome, and confounding factors such as LED differences between groups.

Further exploratory analyses will consider whether exenatide can be thought of as disease modifying by comparing slopes between groups at prespecified periods.

A sensitivity (per-protocol) analysis will be performed for the primary outcome measure and will only include those participants who completed the trial in accordance with the approved protocol.

Results on the primary efficacy outcome will be presented by stratum, according to Hoehn and Yahr stage (≤2.0 vs 2.5), and an interaction between Hoehn and Yahr and treatment will be added to the primary analysis model to investigate whether the effect of treatment differs according to the Hoehn and Yahr stage.

All analyses will be performed by the designated trial statistician.

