Box 1Trial objectivesPrimaryCompare the effectiveness of exenatide once weekly versus placebo on the Movement Disorders Society Unified Parkinson’s Disease Rating Scale (MDS-UPDRS) part 3 motor subscore in the ‘practically defined OFF medication state’ in patients with Parkinson’s disease (PD) (change in the MDS-UPDRS part 3 score reflects accumulation of motor deficit and therefore is a measure of PD motor progression).SecondaryCompare differences at 48 and 96 weeks between the exenatide and placebo trial arms in:MDS-UPDRS part 1, 2, 3 and 4 ON medication scores.Timed walk assessment ON and OFF medication.Montreal Cognitive Assessment.Safety and tolerability of exenatide as indicated by changes in vital signs, weight, clinical laboratory measures and adverse eventsPatient Health Questionnaire.Unified Dyskinesia Rating Scale.Parkinson’s Disease 39 item Quality of Life questionnaire.Levodopa equivalent dose change.A 3-day Hauser diary of PD state (Time-On, Off, Non troublesome Dyskinesia, Troublesome dyskinesia, Asleep).Compare differences in total values over 96 weeks between the exenatide and placebo trial arms in:Health and social care resource use on the modified Client Service Receipt Inventory.Health and social care costs.Paid and unpaid carer costs.Quality-adjusted life-years calculated using the EQ-5D-5L tariff adjusting for baseline.Compare differences between scores at 48 and 96 weeks between the exenatide and placebo trial arms in:MDS-UPDRS part 3 Motor subsection OFF medication score.ExploratoryCompare differences between slopes at prespecified periods between exenatide and placebo trial arms for key outcomes to investigate whether exenatide can be considered disease modifying.EQ-5D-5L, EuroQol- 5 Dimension, 5 Level.

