### Outcomes

#### Safety monitoring

Safety and tolerability of exenatide as indicated by changes in vital signs, weight, clinical laboratory measures and adverse events (AEs) will be recorded and monitored throughout. Each patient will have their pulse, blood pressure and weight documented at screening and at each follow-up visit. Exenatide is known to cause weight loss. Participants’ height will be recorded at screening to enable calculation of body mass index. At each visit, participants are asked to report any AEs that have occurred since the previous visit. AEs may also be detected by the study team reviewing the patient or through notification by the participant’s primary care physician. All AEs will be assessed by a study doctor for their severity, likely relationship to study drug and required action by a study doctor not involved in the blinded assessment of the patient. All SAEs will be recorded and reported to the sponsor regardless of relation to trial treatment. Any suspected unexpected serious adverse reactions will be reported to the sponsor immediately to allow facilitation of unblinding as necessary. All AEs reported will be reviewed by the trial management group (TMG), trial steering group and monitored by an Independent Data Monitoring Committee (IDMC). Unblinding requests from other clinicians responsible for a patient’s care will be handled by the principal investigator (PI) at each site. The PI at each site may also choose to unblind a participant in response to reported AEs as they are reported, if judged to be clinically necessary.

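### As written, the 12-week on-treatment threshold covers all analyses with no exception for safety and tolerability, and it conflicts with the rule that keeps participants who stop treatment in the analysis

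*Protocol article*

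**What the plan says.** The Statistical analysis section of the protocol article opens with a general rule: "All analyses will be undertaken according to a modified intention-to-treat principle in accordance with the randomised intervention". The next sentence defines the set: "The threshold for the analysis population will be participants who complete 12 weeks on treatment and for whom outcomes are available". No exception is stated for safety.

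Box 1 lists, among the secondary objectives to be compared between arms at 48 and 96 weeks, "Safety and tolerability of exenatide as indicated by changes in vital signs, weight, clinical laboratory measures", together with adverse events. The Statistical analysis section adds: "Analyses of the remaining secondary/exploratory outcomes will be undertaken similarly for the difference between groups according to treatment allocation at 48 and 96 weeks".

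Three other places bear on the point:

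- **Safety monitoring** provides for continuous collection: "At each visit, participants are asked to report any AEs that have occurred since the previous visit". It also describes review by the trial management group, the steering group and the independent data monitoring committee.
- **Intervention** names "nausea, vomiting, diarrhoea and weight loss" as examples of common reactions already reported with the drug.
- **Sample size** says that participants who withdraw from treatment stay in the trial, both for follow-up and for data analysis.

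**The concern.** Remaining on treatment for 12 weeks is a post-randomisation event, and tolerability is one of the things that determines it. A safety comparison restricted to people who passed that threshold is conditioned on having tolerated the drug for its first 12 weeks. A participant who stops in week 4 because of vomiting would be absent from the comparison meant to count such stops. In that set, stopping before week 12 is zero in both arms by construction, whatever happened in the trial.

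The article itself names gastrointestinal reactions and weight loss as known effects, so early intolerance is foreseeable. If it were more frequent on exenatide, the reported tolerability of exenatide would look better than the data. In a phase 3 trial with 96 weeks of exposure, the tolerability result is one of the main things a reader will use.

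**Working it through.** **1. Does the stated rule reach safety?**

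| Place | What it fixes |
|---|---|
| Statistical analysis, first paragraph | The principle applies to all analyses; the set is 12 weeks on treatment plus available outcomes |
| Box 1 | Safety and tolerability are a secondary objective compared between arms |
| Statistical analysis, remaining outcomes | Other secondary and exploratory outcomes are handled in the same way as the main ones |
| Safety monitoring | Collection and oversight of adverse events; no population for the final comparison |
| Data management | Independent summaries for the monitoring committee; no population for the final comparison |

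Read together, the first three rows put the tolerability comparison in the 12-week set. No other row gives a different set for it.

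**2. Is the rule consistent with the rest of the article?** Take a participant who stops treatment in week 6 and keeps attending. The Sample size section keeps this person for data analysis. The Statistical analysis section excludes the same person, who has not completed 12 weeks on treatment. Both cannot be followed.

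**3. Do the article's figures give a size?** The sample size reproduces. The baseline-adjusted SD is 13.5 × √(1 − 0.70²) = 9.64. The number per arm is 2 × (1.960 + 1.282)² × 9.64² / 5.0² ≈ 78.1, rounded up to 79. That makes 158 in total against 160 stated, and 160 / (1 − 0.20) = 200. These figures concern efficacy. The 20% attrition is not split by arm, time or reason, so it gives no rate of early stopping for intolerance. The size of any distortion therefore cannot be computed from the documents.

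**4. Illustration under assumed rates.** None of the stop counts below comes from the documents. Assume 100 treated per arm, with 3 late intolerance stops on exenatide and 2 on placebo. Let e₁ and e₀ be the numbers who stop for intolerance before week 12 on exenatide and placebo.

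- All treated: (e₁ + 3)/100 against (e₀ + 2)/100
- 12-week set: 3/(100 − e₁) against 2/(100 − e₀)

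| e₁, e₀ | All treated | Difference (points) | 12-week set | Difference (points) |
|---|---|---|---|---|
| 0, 0 | 3% v 2% | 1.0 | 3.0% v 2.0% | 1.0 |
| 2, 1 | 5% v 3% | 2.0 | 3.1% v 2.0% | 1.0 |
| 5, 1 | 8% v 3% | 5.0 | 3.2% v 2.0% | 1.1 |
| 10, 2 | 13% v 4% | 9.0 | 3.3% v 2.0% | 1.3 |

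The restricted set barely distinguishes the four cases, although the true difference ranges from 1 to 9 points.

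**The case against.** The strongest reply is that the rule was never meant for safety. The Statistical analysis section does not mention safety, tolerability or adverse events. Its set requires available outcomes, and its methods are baseline-adjusted comparisons of scores at 48 and 96 weeks, which do not fit adverse events. Safety has its own heading, and the measures listed under Secondary outcomes include no safety item. The same section uses another population for the per-protocol sensitivity analysis, so its reference to all analyses is not strictly literal. A safety population is also commonly defined in the statistical analysis plan, which the article says will follow.

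Much of this stands. The article is ambiguous, efficacy-only intent is plausible, and the lack of a named safety set would not by itself be a finding. Two things remain. Box 1 does class safety as a between-arm secondary objective, and part of it (weight, vital signs, laboratory measures) can be analysed in the way the section describes. And the article is not silent about the population: it states a general rule without exempting safety, so a later plan with an all-treated safety set would have to depart from that rule as worded.

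A reader might go further and infer that the sponsor has decided to leave early stoppers out of the safety tables, or that early reactions go unrecorded. The documents support neither. No sentence applies the threshold to safety by name, and adverse events are collected at every visit and reviewed by the oversight bodies. What is at risk is the population for the final comparison.

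**Conclusion.** The point holds conditionally. The rule, applied as worded, would remove participants who stop before week 12 for adverse reactions from the tolerability comparison, and it contradicts the Sample size section on those who stop treatment. This rests on reading the reference to all analyses together with Box 1; if the sentence was meant for efficacy only, the defect is one of wording.

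The direction is clear: any bias favours the arm with more early intolerance. A reader might infer that the safety result will be biased towards exenatide, but that requires more early stopping on exenatide, and the documents give no rate for either arm. The figures in the table show the mechanism and are not estimates. Severity is moderate: the primary result, data collection and safety oversight during the trial are unaffected by this point.

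**What to change.** Make three changes to the text, before database lock:

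1. Limit the 12-week on-treatment threshold explicitly to the efficacy analyses.
2. State that safety and tolerability are compared between arms in all participants who received at least one dose of trial medication, including those who stopped before week 12.
3. Reconcile the Statistical analysis and Sample size sections by saying which analyses include a participant who stops treatment before week 12 but stays in follow-up.

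The cost is one or two sentences, carried into the statistical analysis plan. The plan already provides for collecting the data, and the sample size of 200 does not change.

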### Trial design

This is a simple parallel group multicentre phase 3, double-blind, randomised, placebo-controlled trial which includes a 96-week exposure period. Detailed evaluations of all participants will take place at screening, baseline, 24, 48, 72 and 96 weeks (figure 1). Participants will also attend on a 12 weekly basis to collect supplies of Investigational Medicinal Product (IMP). Participants will be randomly allocated to receive either exenatide extended release 2 mg subcutaneous injection (Bydureon) once weekly for 96 weeks n=100, or exenatide extended release placebo subcutaneous injection once weekly for 96 weeks n=100. In addition, participants will be randomised using a minimisation algorithm (with a random element incorporated) balancing by research site, participants with greater (Hoehn and Yahr stage 2.5) or lesser (Hoehn and Yahr stage 2.0 or less) PD severity (in the ON medication state), and participation in the substudies (remote monitoring, imaging or not participating).

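### The primary analysis set requires 12 weeks on study drug, a post-randomisation condition that may depend on allocation and conflicts with the instruction to keep patients who stop treatment in the analysis

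*Protocol article*

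**What the plan says.** The Statistical analysis section sets one principle for all analyses: "All analyses will be undertaken according to a modified intention-to-treat principle in accordance with the randomised intervention". It then gives the entry condition: "The threshold for the analysis population will be participants who complete 12 weeks on treatment and for whom outcomes are available". Two requirements are joined here, a minimum time on treatment and availability of outcomes.

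The Sample size section addresses patients who stop the drug: "Participants who withdraw from trial treatment should remain in the trial for the purpose of follow-up and data analysis". It attaches no minimum exposure.

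The only sensitivity analysis named is per-protocol, which "will only include those participants who completed the trial in accordance with the approved protocol".

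Two further statements matter. The Intervention section says patients will be told about "common adverse reactions previously reported, for example, nausea, vomiting, diarrhoea and weight loss". The Trial design section gives the schedule: "Detailed evaluations of all participants will take place at screening, baseline, 24, 48, 72 and 96 weeks".

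**The concern.** Randomisation makes the two complete groups comparable. A subset chosen by something that happens afterwards keeps that comparability only if the selection is the same in both arms or unrelated to outcome. Staying on an injectable drug with known gastrointestinal effects for 12 weeks need not meet either condition. Blinding does not secure it, because tolerability can differ between arms whether or not anyone knows the allocation. Analysing the remaining patients in their allocated arms does not bring back those who were removed.

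The rule is also more than a need for data. Outcome availability is a separate requirement in the same sentence. A patient who stops at week 8 and then provides OFF scores at weeks 24, 48, 72 and 96 has every score the mixed model needs, and is still excluded.

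At stake is the meaning of the confirmatory result. With this set the trial compares patients who stayed on treatment for at least 12 weeks in each arm, and no longer estimates the effect of being assigned to exenatide. It would also leave unused OFF-state scores that the Sample size section says are to be collected for analysis.

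**Working it through.** **1. The two sections side by side**

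| Patient | Sample size section | Statistical analysis section |
|---|---|---|
| Stops drug after week 12, stays in follow-up | Analysed | Analysed |
| Stops drug before week 12, stays in follow-up | Analysed | Excluded |
| Stops drug before week 12, leaves before week 24 | No post-baseline OFF score | Excluded |

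The conflict is confined to the second row. In the third row the rule makes no practical difference, because the first post-baseline detailed evaluation is at week 24.

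**2. The plan's own figure**

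Inputs, from the Sample size section: "The calculations assume a common SD of 13.5, and a correlation of 0.70 between baseline and follow-up MDS-UPDRS measurements"; the design is "sufficient to detect a difference of 5.0 MDS-UPDRS part 3 points in the OFF medication state" with 90% power, significance level 0.05, 160 evaluable and 20% attrition. Sidedness is not stated; two-sided is assumed.

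- Baseline-adjusted SD = 13.5 × √(1 − 0.70²) = 13.5 × √0.51 = 9.64.
- n per arm = 2 × (1.96 + 1.2816)² × 9.64² / 5.0² = 78.1, rounded up to 79, so 158 in total against the stated 160.
- At 80 per arm, SE = 9.64 × √(2/80) = 1.524, and power = Φ(5.0/1.524 − 1.96) = 90.7%.
- 160 / 0.80 = 200 recruited.

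The stated design is reproduced. This neither supports nor weakens the point about the population, but it supplies the SE used below.

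**3. What the rule could do when the drug has no effect (illustration)**

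The document gives no rate of stopping before week 12, so the rates and the outcome gap are assumptions. Let e be the share of an arm excluded by the rule, and D the number of points by which excluded patients would have scored worse than retained ones. If the full arm has mean μ, the retained patients have mean μ − e × D. Higher scores are worse, so the spurious advantage for exenatide is (e on exenatide − e on placebo) × D. With b = advantage / 1.524, the two-sided type I error is Φ(−1.96 + b) + Φ(−1.96 − b).

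| Excluded, exenatide vs placebo | D | Spurious advantage | Type I error |
|---|---|---|---|
| 5% vs 5% | any | 0 | 5.0% |
| 5% vs 2% | 5 | 0.03 × 5 = 0.15 | 5.1% |
| 10% vs 2% | 5 | 0.08 × 5 = 0.40 | 5.8% |
| 15% vs 5% | 5 | 0.10 × 5 = 0.50 | 6.2% |
| 15% vs 5% | 10 | 0.10 × 10 = 1.0 | 10.1% |

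The last row is an extreme case. If excluded patients would have scored better, the sign reverses.

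**4. What including early stoppers could do when the drug works (illustration)**

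Suppose the effect is 5.0 points in patients who continue and nil in early stoppers on exenatide, with 160 evaluable. The average effect is 5.0 × (1 − share stopping early).

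| Early stoppers on exenatide | Average effect | Power at 160 | Evaluable / recruited for 90% |
|---|---|---|---|
| 5% | 4.75 | 87.6% | 174 / 218 |
| 10% | 4.50 | 83.9% | 194 / 243 |
| 15% | 4.25 | 79.6% | 218 / 273 |

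The gap between 5.0 and these averages is a difference between two target effects, tolerators versus all assigned. It should not be read as bias alone.

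**The case against.** The strongest reply is that the problem may be small. The document lists common reactions but does not say that they lead patients to stop before week 12, and gives no stopping rate for either arm. Patients who stop and also leave before week 24 contribute no outcome under any definition, so the rule bites only on early stoppers who stay in follow-up, an unknown fraction. With a 5-point gap the illustrated bias is at most 0.5 points against a 5.0-point target. All of this stands, and it limits the claim about size. It does not justify an exposure condition in the primary set.

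It can also be said that the Sample size sentence is a general retention instruction, and that the two sections agree for anyone stopping after week 12. That is right. The conflict concerns earlier stoppers only, but for them the wording cannot be followed both ways.

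Three stronger readings are tempting and are not supported:

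- A reader might infer that exclusions will be unequal between arms and will favour exenatide. The document shows only that they may be unequal, and the direction depends on how excluded patients would have scored.
- A reader might infer that these exclusions come on top of the 20% attrition and so erode power. The article describes attrition as withdrawal or loss to follow-up and does not define evaluable, so early stoppers may already be counted in the 20%. No power loss should be charged to the rule on this ground.
- A reader might infer that no analysis of all randomised patients is planned anywhere. The full analysis plan is not shown. The point rests on the rule that the article states, and the per-protocol analysis matters only because it is narrower and so cannot test that rule.

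**Conclusion.** The population rule is wrong as written. It applies a post-randomisation exposure condition to the confirmatory comparison, it is separate from data availability, and it conflicts with the Sample size section for patients who stop before week 12 and remain in follow-up. This is a stated rule, so an analysis plan that follows the article would inherit it.

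Its numerical consequence is unknown. Bias is nil if exclusions are balanced and unrelated to outcome. Under the assumed exclusion rates and a 5-point gap it is about 0.15 to 0.5 points, with two-sided type I error of about 5.1% to 6.2% at 80 per arm. These figures rest wholly on assumptions and show only the order of magnitude. The case for changing the rule rests on preserving the randomised comparison and on the internal conflict.

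**What to change.** - Define the primary analysis set as all randomised participants, analysed as allocated whatever their time on study drug, using every available post-baseline OFF score, including scores after treatment stops.
- Keep the 12-week-on-treatment set and the per-protocol set, both labelled supplementary.
- Reconcile the Statistical analysis section with the Sample size section, so that both say the same about patients who stop before week 12.

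The follow-up is already required, so no new data collection is needed, and the article has the analysis plan approved before database lock, which leaves room for the change. The 160 evaluable and 200 recruited need not change merely because these patients are included, since the article puts no exposure condition on evaluable. There is a price: if early stoppers gain no benefit, the estimated effect will be smaller and power for it lower, for example 4.75 points and about 88% power at 160 evaluable with 5% early stoppers on exenatide. That consequence should be stated openly when the change is made.
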